**Postpartum period**			
Mental health education	2 weeks postpartum	Knowledge of postnatal health care and symptoms of perinatal depression. Review the concept of CBT	Self-evaluation and goal setting
Behavioral activation	3 weeks postpartum	Make use of positive or negative reinforcement	Record positive or negative behavior and make a list of behavior which should be reinforced. Set up a reward system for carrying out a mission
Cognitive restructuring	4 weeks postpartum	Recognition of negative automatic thoughts and strategies to solve the problems	Make a list of personal typical negative automatic thoughts and record automatic thoughts within the past week. Awareness of cognitive bias
Summary and relapse prevention	5 weeks postpartum	Make a summary of what have learned. Provide strategies for preventing relapse	Make a future plan and practice mindfulness
**Additional modules**			
Worry and anxiety	37 weeks of gestation	Problems in regard to pregnancy, labor and caring newborn	Share concerns about labor and childcare and find out ways to solve the problem
Sleeping problem	38 weeks of gestation	Provide problem solving strategies	Record sleeping habits, improve sleeping environment, and restrict time for sleep
Interpersonal relationship	1 week postpartum	The way of communication and psychological education of shifting roles and responsibilities in home	The relationship between parents and understanding the role of a mother. Skills to improve mood and cope with other family members
Mother-infant relationship	1 week postpartum	Psychological support for new mothers	Share feelings and give feedback about difficulties in being a mother

#### Usual care control

Women in both groups will receive standard antenatal depression care including maternal self-care educational videos and mental health assessment. The educational videos include information regarding labor and delivery, postpartum self-care strategies, infant care, and breastfeeding. Women are assessed for depression and anxiety symptoms using the PHQ-9 and GAD-7 respectively at 6 weeks postpartum via the app. Women with a PHQ-9 score > 14 or > 1 in the last PHQ-9 item related to self-harm will be referred to a psychiatrist for further assessment. No concomitant treatments would be prohibited during this trial. However, we will mark participants who have been referred to psychiatrist for drug treatment and complete follow-up data. Analysis would be conducted for all participants enrolled as well as participants excluding those receiving drug treatment.

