#### Exclusion criteria

Exclusion criteria include (1) active suicidal ideation, (2) severe psychopathology (e.g., schizophrenia), and (3) currently receiving treatment for depression and anxiety including other psychotherapy or medication.

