All data will be extracted from the security server of the main center and incorporated in a single Microsoft Excel database through the computer system. The original data will be verified by researchers before analyzed and non-conforming data will be excluded with certain reasons listed. For analysis, descriptive statistics of continuous variables will be represented as means and standard deviations or medians and inter quartile ranges. Categorical variables will be expressed as frequencies with proportions. Differences of continuous variables with normal distribution between groups will be tested by Student’s *t*-test, whereas Mann-Whitney *U* test will be applied to variables with skewed distribution. Categorical variables will be tested by chi-square test. Demographic and medical characteristics at baseline will be analyzed for whether they are equivalent between two groups; otherwise, a subgroup analysis will be performed for adjusting confounding factors. Main analyses will be conducted using intention-to-treat (ITT) model, in which all participants will be included based on random allocation regardless of study completion. For outcomes collected at multiple time points, repeated measures design using generalized estimating equation (GEE) models will be conducted to fit outcomes that are measured at each time point, so that all the participants might contribute to the analyses, even if there were missing data at some of the follow-up points. In addition, statistical analysis of the baseline characteristics of those who remain in the study and those who are lost to follow-up will also be conducted to explore whether there is differential drop out. All statistical analyses will be performed using the R software (version 4.0.2) or other statistical software packages if necessary. Differences will be considered significant if the two-sided p value is less than 0.05.

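### The repeat analysis that leaves out women on drug treatment selects on a consequence of the primary outcome, so it is not a comparison of randomised groups

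*Protocol article*

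**What the plan says.** All references are to the protocol article.

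- **Usual care control**, on timing: "Women are assessed for depression and anxiety symptoms using the PHQ-9 and GAD-7 respectively at 6 weeks postpartum via the app".
- **Usual care control**, on referral: "Women with a PHQ-9 score > 14 or > 1 in the last PHQ-9 item related to self-harm will be referred to a psychiatrist".
- **Usual care control**, on other treatment and follow-up: "No concomitant treatments would be prohibited during this trial", but "we will mark participants who have been referred to psychiatrist for drug treatment and complete follow-up data".
- **Usual care control**, on analysis sets: "Analysis would be conducted for all participants enrolled as well as participants excluding those receiving drug treatment".
- **Exclusion criteria** bar women "currently receiving treatment for depression and anxiety including other psychotherapy or medication".
- **Primary outcome measure** defines the primary outcome as the prevalence of depression by PHQ-9 at 6 weeks postpartum. It lists cut-offs of 5, 10 and 15, and repeats the PHQ-9 at 12, 24 and 52 weeks.
- **Sample size and statistical analysis** makes intention to treat the main analysis, "in which all participants will be included based on random allocation regardless of study completion".

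**The concern.** The second analysis set is defined by something that happens after randomisation. Women in treatment are barred at entry, so any drug treatment for depression among participants is new. The route the protocol describes runs from the 6-week PHQ-9 to psychiatric referral to drugs. A woman can therefore leave the set because of her value on the primary outcome.

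A difference between arms in that set mixes the effect of iCBT with the effect of who was removed. The two analyses are announced side by side in one sentence, which gives neither a rank and does not say which outcomes the second one serves. A reader of the results could take the drug-free comparison as the purer estimate of the iCBT effect, which it is not.

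**Working it through.** **Step 1. What the score trigger selects.** A PHQ-9 above 14 on an integer scale means 15 or more. That meets each of the listed cut-offs (5, 10, 15). So every woman removed through the score trigger is a primary-outcome case, whichever cut-off defines depression. The self-harm item is a separate trigger and need not imply a case.

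**Step 2. Timing.** Drugs prescribed because of the 6-week score start after it and cannot have changed it. Removing these women takes no contamination out of the 6-week result; it only deletes cases. At 12, 24 and 52 weeks drugs may well affect the score, but whether a woman was medicated depends on her earlier state, which iCBT may have altered.

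**Step 3. Inputs for size.** The planning rates are 47.3% (standard care) and 22.2% (CBT), a difference of 47.3 − 22.2 = 25.1 points. They reproduce the plan's own sample size: (1.960 + 1.282)² × (0.473 × 0.527 + 0.222 × 0.778) / 0.251² = 70.4, so 71 per arm; 71 / 0.80 = 88.75, so 89 per arm and 178 in total. These are therefore the rates the plan works with.

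*Assumed, not in the documents:* a share q of depressed women in an arm receives drugs and is excluded, and no non-depressed woman is.

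**Step 4. Formula.** An arm with depression rate p loses p·q of its women. The rate among the rest is p(1 − q) / (1 − pq). The odds become (1 − q) times the original odds, so the odds ratio is multiplied by (1 − q for iCBT) / (1 − q for control).

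**Step 5. Equal q in both arms.**

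| q | Removed, control / iCBT | Rates after | Risk difference | Risk ratio | Odds ratio |
|---|---|---|---|---|---|
| 0 (all women) | 0 / 0 | 47.3% / 22.2% | 25.1 | 0.469 | 0.318 |
| 0.3 | 14.2% / 6.7% | 38.6% / 16.6% | 21.9 | 0.431 | 0.318 |
| 0.5 | 23.7% / 11.1% | 31.0% / 12.5% | 18.5 | 0.403 | 0.318 |

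For q = 0.3: 0.473 × 0.7 / (1 − 0.1419) = 0.386, and 0.222 × 0.7 / (1 − 0.0666) = 0.166. At 150 per arm, q = 0.3 removes about 21 controls and 10 iCBT women.

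**Step 6. Unequal q.** Suppose iCBT also reduces severity, so that 40% of depressed controls but 20% of depressed iCBT women score above 14, and 50% to 100% of those are medicated. Then q is 0.2 to 0.4 for control and 0.1 to 0.2 for iCBT. The risk difference becomes 21.4 to 16.4 points, the risk ratio 0.489 to 0.531, and the odds ratio 0.318 × 0.9/0.8 = 0.358 to 0.318 × 0.8/0.6 = 0.424. All three measures now move toward no effect.

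**Step 7. No true effect (47.3% in both arms).** With equal q the difference stays at 0. With the q values of Step 6 it becomes 2.9 to 6.8 points against iCBT. With q = 0.1 for control and 0.3 for iCBT it becomes 44.7% − 38.6% = 6.1 points in favour of iCBT.

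**The case against.** **It is only an additional analysis.** This stands. The exclusion is run as well as the analysis of all participants, intention to treat is named as the main analysis, and marked women are still followed. A reader might infer a breach of intention to treat; the text does not support that, and the main result is the same in every scenario above.

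**The exclusion may be meant for the later outcomes.** This is plausible, because drugs started after the 6-week visit could affect the 12- to 52-week scores. But the protocol does not limit it to those outcomes, and there the selection problem remains.

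**Selection is not purely on the primary outcome.** Also true. A psychiatrist's assessment and actual prescribing lie between the score and the exclusion, the self-harm item is a second trigger, and other treatment is not prohibited, so some women may start drugs before 6 weeks. The score is the main written route, not the only one.

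**Differential referral is not shown.** A reader might infer that therapist contact leads to more referral in the iCBT arm and so to a false benefit. The documents do not say this. The same PHQ-9 rule applies to both arms, scores are reviewed by an assistant outside other trial activities, and research assistants make the referrals. The 6.1-point figure in Step 7 rests entirely on an assumed split, and a different split gives the opposite sign.

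**Data exclusions.** The statement that "non-conforming data will be excluded with certain reasons listed" might be read as a second way for women to drop out of the analysis. It speaks of data found at verification, not of participants, and its definition is detail that an article commonly leaves to fuller documents. No bias can be shown from it.

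**Conclusion.** The concern holds for the analysis that excludes drug-treated women, and only for that. It conditions on a post-randomisation event set off largely by the 6-week PHQ-9, so it is not a randomised comparison. At 6 weeks it has no rationale for women treated because of that score.

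At the planning rates, with an assumed equal 30% to 50% of depressed women medicated, the risk difference loses 3.2 to 6.6 points (25.1 to 21.9 or 18.5). The true share is not in the documents. It may well be smaller, because referral needs a score above 14 or the self-harm trigger, and then a prescription.

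A reader might infer that the exclusion always understates a real effect. That is so for the risk difference under equal shares, but the odds ratio is then unchanged and the risk ratio moves away from 1. The protocol article fixes no effect measure, so no single direction can be claimed. The main intention-to-treat result is not in question.

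**What to change.** 1. State that the main estimate at every time point keeps all randomised women, whatever drug treatment they start later.
2. Replace the exclusion with a sensitivity analysis of the PHQ-9 depression outcome in all randomised women. A woman who started drug treatment for depression before an assessment counts as depressed at that assessment. A woman treated only after the 6-week score stays in the 6-week analysis with her observed score.
3. If the exclusion analysis is kept, do not apply it to the 6-week outcome, and label it supplementary and non-randomised. Report the number excluded in each arm beside it.

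The cost is a change of wording and one further model. The protocol already marks the women concerned; the start date of treatment must be recorded with the mark if it is not already. The downside is that the composite treats medication as failure, and it can itself be distorted if referral differs between arms, so it should remain a sensitivity analysis.

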#### Therapist training and treatment fidelity

Graduate-level trainees of psychology will be iCBT therapists and provided with training and supervision by a registered psychologist with experience in depression management. Training consisting of a 2-day workshop prior to engaging in the intervention and a manual detailing weekly content for iCBT was created to assist therapists. Intervention adherence is defined by proportion of modules completed within 5 weeks postpartum. Intervention engagement will be defined as length of time spent on the modules. This will include (1) frequency of visits to iCBT modules, (2) duration of time spent on each module, and (3) rate of assignment submission.

## Outcomes

Primary and secondary outcomes were chosen based on previous CBT studies and other postpartum depression prevention trials. The aim is to include outcomes that will evaluate effect of the iCBT intervention on depression symptoms that started before childbirth and prevent the development of depression across the first year postpartum. Refer to Table 2 for the schedule of study assessments measured at each follow-up time point to 12 months postpartum.

**Table 2 Tab2:** Outcome measurement and timing of data collection

Data collection		Time of measurement					
Content	Assessment criteria	Baseline	Postpartum				
			6 weeks	3 months	6 months	9 months	1 year
Demographics	Questionnaire form	**×**					
Primary outcomes							
Depression	PHQ-9		**×**				
Secondary outcomes							
Depression	PHQ-9			**×**	**×**		**×**
Anxiety	GAD-7		**×**	**×**	**×**		**×**
Sleep Quality	PSQI			**×**	**×**		**×**
Social Support	MSPSS				**×**		
Parenting satisfaction	PSI-SF					**×**	
Co-parenting relationship	BCRS					**×**	
Infant development	DDST			**×**	**×**		**×**

## Primary outcome measure

The primary outcome is prevalence of depression at 6 weeks postpartum using the PHQ-9, which is a 9-item self-report measurement used to assess depressive symptoms over the last 2 weeks [27]. Each item is scored from 0 (not at all) to 3 (nearly every day) for a total score ranging from 0 to 27. Scores of ≥ 5, ≥ 10, and ≥ 15 represent mild, moderate, and severe levels of depressive symptoms respectively. Psychometric properties and sensitivity to change are well documented [38]. We will re-administer the PHQ-9 at 12, 24, and 52 weeks postpartum to evaluate the longer-term treatment effect of iCBT and the prevention of new cases of depression.

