## Abstract

**Background:**

Depression and anxiety are common among pregnant women. Internet-delivered psychological therapies such as cognitive behavioral therapy (iCBT) have been developed to increase accessibility and address common help-seeking barriers, especially during pandemic period. The objective of this trial is to evaluate the short-term and long-term effects of iCBT on reducing depressive symptoms among pregnant women during the COVID-19 pandemic with the overall goal of preventing depression recurrence in the first 12 months postpartum.

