## Sample size and statistical analysis

Based on a previous trial, Chinese pregnant women with depressive symptoms who received CBT delivered face-to-face showed significantly lower rates of postpartum depression than those who received standard antenatal care (22.2% vs 47.3%, *P* = 0.001) [25]. We estimate that a sample size of at least 178 (89 per group, assuming 20% loss to follow-up) is required to detect a 25% reduction in depression symptoms at 6 weeks postpartum on based on a 90% power to detect differences between groups and a two-sided significance level of 0.05. Considering the possible decreased efficacy due to CBT delivered by internet rather than face-to-face, we aim to recruit 300 participants in this study.

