## Risk management strategies

Several strategies will be implemented to mitigate potential risk. First, potential participants who endorse self-harm on the EPDS or PHQ-9 undergo a suicide risk assessment. Those who score positive for suicide ideation will be referred to the emergency department or a mental health specialist for immediate assessment. As discussed in the consent form to ensure safety, the emergency department or a mental health specialist will be contacted on the participant’s behalf if necessary. Considering the intervention is a non-pharmacological treatment, adverse effects due to the intervention are negligible. However, severe adverse events including suicidal behaviors or deaths will be recorded in case report form and reported in the future published manuscript. Participants are allowed to leave the study at any time based on their personal willingness. Research assistants are required to complete the withdrawal report form in detail.

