## Implications

Faced with increased risks of psychological distress during the COVID-19 pandemic and higher rates of depression and anxiety among pregnant women specifically, there is an urgent need for the development of effective and easily accessible treatment options. Here, we describe the protocol for a RCT that aims to evaluate the efficacy of iCBT in the treatment of antenatal depression with the goal of preventing depressive symptoms across the first year postpartum. Compared with the traditional face-to-face psychological treatment, iCBT addresses many treatment and help-seeking barriers and may be an effective treatment for antenatal depression during a major public health emergency. To date, most studies examining iCBT among depressed pregnant or postpartum women have demonstrated efficacy in a small scale with a limited follow-up period and no assessment of infant outcomes [24, 25, 39, 40]. To overcome these limitations, we plan to recruit 300 pregnant women with depressive symptoms from five diverse settings and will follow them to 1 year postpartum to evaluate longer-term impact on both women and their infants. If positive results from this trial are obtained, it will provide strong evidence for the effectiveness of iCBT in the treatment of antenatal depression with the goal of preventing the development of depression across the first year postpartum. Furthermore, if proven effective, this intervention has the potential that can be provided during major public health emergencies.

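### The randomised data can show postpartum PHQ-9 prevalence, but not prevention of new cases or recurrence, nor an effect on depression during pregnancy

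*Protocol article*

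**What the plan says.** All references are to the protocol article.

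- **Primary outcome measure.** The primary outcome is the proportion of women depressed on the PHQ-9 six weeks after birth. The scale is repeated at 12, 24 and 52 weeks "to evaluate the longer-term treatment effect of iCBT and the prevention of new cases of depression". Cut-points of 5, 10 and 15 are listed, and the article names none of them as the case definition.
- **Outcomes, Table 2.** The table is introduced as the "schedule of study assessments measured at each follow-up time point to 12 months postpartum". In its baseline column only demographics is marked. PHQ-9 and GAD-7 begin at 6 weeks postpartum and every other outcome begins later.
- **Participant eligibility; Participant screening, recruitment, and enrolment.** Every participant has an EPDS score above 9, taken at 28 to 34 weeks of gestation, before randomisation.
- **Abstract, Background.** The trial is run "with the overall goal of preventing depression recurrence in the first 12 months postpartum".
- **Implications.** If the result is positive, "it will provide strong evidence for the effectiveness of iCBT in the treatment of antenatal depression".
- **Risk management strategies.** Here "potential participants who endorse self-harm on the EPDS or PHQ-9 undergo a suicide risk assessment", which suggests a PHQ-9 before enrolment that Table 2 does not show.

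**The concern.** Three claims go further than comparing postpartum prevalence. Prevention of new cases needs women known to be free of depression at the start of the risk period. Prevention of recurrence needs a remission followed by a return. Treatment of antenatal depression, read as an effect during pregnancy, needs an outcome in both arms before birth. The schedule supplies none of these, in a cohort selected for already having symptoms.

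What is at stake is interpretation. A lower 6-week prevalence under iCBT could reflect faster resolution of existing symptoms, fewer relapses or fewer onsets. As the aims now stand, one result could be read as support for all three.

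**Working it through.** **1. The plan's own figure.** Inputs from Sample size and statistical analysis: 47.3% under standard care and 22.2% under CBT, "based on a 90% power to detect differences between groups", "a two-sided significance level of 0.05", and 20% loss.

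Unpooled two-proportion formula: n = (1.960 + 1.282)² × [0.473 × 0.527 + 0.222 × 0.778] / (0.473 − 0.222)²
= 10.507 × 0.4220 / 0.0630 = 70.4, so 71 per arm.

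Inflated for loss: 71 / 0.80 = 88.75, so 89 per arm and 178 in total. The stated figure is reproduced. It uses postpartum rates only, so no baseline PHQ-9 enters it.

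At the recruitment target: 300 × 0.80 / 2 = 120 evaluable per arm. Power for 47.3% against 22.2% is then 98.6%. The missing baseline PHQ-9 changes neither sample size nor power.

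**2. Each aim against the schedule.**

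| Aim | What it needs | What is scheduled |
|---|---|---|
| Lower postpartum depression | PHQ-9 in both arms after birth | 6 weeks, 3, 6 and 12 months: identified |
| New cases | Depression-free status at the start | All enter with EPDS > 9: not identified |
| Recurrence | Remission, then return | No remission check before 6 weeks: not identified |
| Effect during pregnancy | Antenatal outcome in both arms | None: not identified |

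**3. Length of the unobserved period.** Screening is at 28 to 34 weeks. Assuming birth at 40 weeks, the time from enrolment to the 6-week visit runs from (40 − 34) + 6 = 12 weeks to (40 − 28) + 6 = 18 weeks. Each week earlier or later at birth shifts both ends by one week. Three of the seven core modules are delivered in this period before birth. The Intervention section mentions outcome monitoring within modules, but modules go to the iCBT arm only, so this yields no randomised comparison.

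**4. Coverage after birth.** Each PHQ-9 refers to the previous 2 weeks. Four visits cover 4 × 2 = 8 of the 52 postpartum weeks (8 / 52 = 15%). Prevalence at separate visits is therefore not a measure of recurrence over the year.

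**5. Onset after 6 weeks.** The serial PHQ-9 can describe onset among women who are non-cases at 6 weeks. That group is defined after randomisation by the outcome the treatment is meant to change, so comparing arms within it is not a randomised comparison.

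**The case against.** The strongest defence is that the core question is intact, and that stands. The randomised comparison of postpartum prevalence needs no baseline PHQ-9. The timing is also coherent: core modules run to 5 weeks postpartum, so 6 weeks is the first assessment after they end, and an antenatal outcome would fall mid-treatment. Some of the wording is aspirational; recurrence appears as an overall goal in the abstract and not in Study objectives. The Implications sentence can be read as meaning women with antenatal symptoms assessed after birth, which is the wording proposed below.

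Three stronger readings are tempting and are not supported:

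- *That no baseline depression measure exists, or that no woman has a baseline PHQ-9.* Every woman has a screening EPDS before randomisation. Table 2 is also not a full list of baseline data: it omits the EPDS and the pregnancy complications mentioned under Data management. The supportable statement is that no baseline PHQ-9 is scheduled in Table 2. For the same reason, the PHQ-9 mention in Risk management strategies is an unresolved ambiguity, not a proven contradiction.
- *That the plan breaks randomisation by analysing only women well at 6 weeks.* No such analysis is planned. The article specifies intention-to-treat with GEE across visits.
- *That adding a baseline PHQ-9 would cure the problem.* With 203 women already randomised, it could be missing for at least 203 / 300 = 68% of the target. A single PHQ-9 near the time of a positive EPDS would still not separate new, recurrent and persistent depression.

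**Conclusion.** The point holds in limited form. The trial can validly estimate the effect of iCBT on postpartum PHQ-9 prevalence among women who screened positive in pregnancy. It cannot show an effect on depression during pregnancy, and it cannot separate new or recurrent depression from persistent depression. The claims in Primary outcome measure, the abstract and Implications go beyond this.

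The primary sample size and power are unaffected. The size of the problem is the number of stated claims the design does not identify, which is three, together with a gap of roughly 12 to 18 weeks without a comparative outcome.

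This rests on Table 2 being complete for outcomes, on birth near 40 weeks for the length of the gap, and on no antenatal remission check existing beyond what the article describes.

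**What to change.** 1. **Primary outcome measure.** Replace prevention of new cases with two outcomes in all randomised women: PHQ-9 case prevalence at each visit, and the proportion ever at or above the case threshold at a scheduled visit between 6 weeks and 12 months. Fix one PHQ-9 threshold for both. State that onset after 6 weeks among women who are non-cases at 6 weeks is descriptive only.
2. **Sample size and statistical analysis.** Name the screening EPDS score as the baseline severity measure and include it as a covariate in the models already planned.
3. **Abstract and Implications.** Limit the recurrence and antenatal-treatment wording to postpartum depression in women with antenatal symptoms.
4. **Risk management strategies and Table 2.** Reconcile the two by stating whether potential participants complete a PHQ-9 before enrolment. This concerns the data schedule only, not the risk procedure itself.

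Record the changes in an amendment dated before any comparison by arm. No new data collection is needed. The costs are narrower claims and, for the ever-case outcome, a pre-stated way of handling missed visits, since a woman with no observed case but a missed visit has unknown status.
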